## Methods: data collection, management and analysis

### Data collection methods and management {25a}

All data storage and collection will occur in accordance with the University of Manitoba research ethics boards standards. Participants will be informed during the consent process that they are free to withdraw at any time. Additionally, the study coordinators and principal investigators may remove a participant from the LightBEAM trial if they violate the forum’s terms of use.

Questionnaire data will be collected on REDCap. Data captured within the LightBEAM app (i.e., participant weekly questionnaire response and forum posts) will be stored on a Firebase Server and data storage located in Montreal, Canada in the Google cloud.

### Statistical methods {27a, b}

Statistical analysis will occur on both IBM Statistical Package for the Social Sciences (SPSS) and Mplus 8.4. Prior to data analysis, data files will be reviewed to ensure participant questionnaire data are in the expected range and scored correctly. Missing data will be address using an intent-to-treat analysis and maximum likelihood estimation.

#### Aim 1

The feasibility of the LightBEAM program will be evaluated through examining a variety of program specific metrics including participant app usage, program attrition, and self-report implementation metrics. See Table 3 for a full list of pre-specified success criteria. Descriptive statistics (e.g., frequencies, means) will be used to examine participant program implementation metrics. Additionally, a series of qualitative questions will evaluate feasibility and acceptability in the focus groups, building off and extending the understanding of the numerical data. A manifest content analysis will be utilized to quantify and analyze qualitative focus group data. Guided by the feasibility and acceptability framework (see Sekhon et al. [31]), this approach will involve determining unit of analysis and coding rules that are applied to focus group transcripts. Next, a coding team will apply the relevant codes and share initial impressions [6]. Candidate codes will be considered and redefined in a iterative processes. Next, the coding framework will be trialed and finally first pass coding will be reviewed for comprehensiveness, patterning, and mapping.

**Table 3 Tab3:** Overview of LightBEAM weekly content

Week	Mental Health Topic	Parenting Topic
1	Values (Defining Values and Finding Motivation)	Family Values (finding and following your values)
2	Emotions + Function	Loving your whole child
3	Mindful Emotion Awareness	Helping your child name & understand their emotional experiences
4	Understanding your emotions	Emotions in the Moment (Tantrums + Coping Thoughts)
5	Emotional ARC and doing the unexpected	Meeting your child in their emotions ARC
6	Managing Emotions Reactions	Co-regulating DT + TIPP Skills
7	Anticipating Emotions and challenging moments	Pre-teaching and successful routines
8	Cognitive flexibility	Flexibility through transitions
9	Interpersonal effectiveness and clarifying priorities	Clarifying family boundaries and RESET
10	Navigating Conflict	Conflict management and STOP skills
11	Boundary setting to make space for everything else	Memory making with your kiddo
12	Staying well and moving forward	Recipe for wellness

#### Aim 2

All eligible participants must present with at least one elevated symptom of concern across parental anxiety (GAD-7), depression (PHQ-9), anger (PROMIS) and/or parenting stress (PSI). Based on which metric(s) participants screen in as being elevated, an individualized composite primary score will be created whereby we examine whether there is a statistically significant change in elevated symptoms of concern across assessment time points. To examine the efficacy of the LightBEAM program in improving parental outcomes, a multi-level model with random intercepts will be utilized to assess the effect of treatment over time based on conditions. An intent to treat approach will be followed such that all randomized participants are included in analysis, regardless of completion.

Specifically, we will examine pre-to-post-to follow up program changes in primary and secondary outcomes. Such analysis will allow us to examine the efficacy of the LightBEAM program compared to other community resources. Program engagement metrics (e.g., number of videos watched, see Table 4) will also be included as moderators to probe whether participant changes are due to program engagement. This dosage analysis will be an exploratory analysis.

**Table 4 Tab4:** Aim 1 feasibility and acceptability metrics

	Indicator	Benchmark	Rational
Recruitment Rate	Number of parents recruited per month	Approx. 50 parents	We want at least 50 parents in the forum to ensure maximum engagement
Retention Rate	% of parents with follow up data	> 70% of parents with follow up data	Average retention rate amongst previous MOOI’s is 70%
Forum Use	# of posts and comments made on the forum	> 50% of users engage at least once in the forum (i.e., through posting, responding or interacting with a message)	This is an exploratory outcome. Based on previous work that showed 57% engagement in the BEAM forum
Videos watched	% of videos watched at least 50% of the way through	Participation in > 50% of the LightBEAM Content	Utilizing same benchmark (e.g., 50%) used in previous BEAM pilot studies [13]
Symptom tracking	# of weekly surveys completed	Participation in > 50% of symptom tracking exercises	Based on benchmark used in previous BEAM pilot studies
Acceptability	Self-reported implementation metrics	Score > 4 considered strong implementation	Based on benchmark used in previous BEAM pilot studies

The acceptability aim is assessed using an online questionnaire designed for app based mental health programs. See Appendix 2 for a full list of questions

#### Aim 3

To examine the characteristics of families who benefited most from the LightBEAM program, demographic characteristics and service-related variables will be included as moderators in the same multi-level model discussed in objective 2. Sociodemographic factors (i.e., age, marital status, number and age of children) will also be examined to determine for whom the LightBEAM program is best suited for.

On an exploratory basis, we will use regression to examine the effects of several potential moderators (e.g., child age, severity of child baseline problems, previous caregiver mental health diagnosis, household chaos, gender of caregiver) to understand how various social groups differentially experience the program.

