### Definition of analysis population related to protocol non-adherence and methods to handle missing data {27c}

The LightBEAM program will employ an intent-to-treat analysis using maximum likelihood estimation, whereby all participants, regardless of study completion and adherence, will be included in analysis based on their initial randomization. To account for treatment adherence, de-identified analyses will be conducted using only data from participants who completed the LightBEAM intervention.

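### Maximum likelihood is the only missing-data method named, with no stated role for app use; if low users both drop out more and benefit less, the LightBEAM effect may be overstated

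*Protocol article*

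**What the plan says.** The section Statistical methods {27a, b} gives one sentence on missing data: "Missing data will be address using an intent-to-treat analysis and maximum likelihood estimation". Section {27c}, on the analysis population and missing data, repeats it: "The LightBEAM program will employ an intent-to-treat analysis using maximum likelihood estimation". Neither place lists the variables that enter the likelihood.

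Under Aim 2 the efficacy model is specified: "a multi-level model with random intercepts will be utilized to assess the effect of treatment over time based on conditions". Everyone randomised is included. App use enters the efficacy work in one way: "Program engagement metrics (e.g., number of videos watched, see Table 4) will also be included as moderators", in order "to probe whether participant changes are due to program engagement". The article adds: "This dosage analysis will be an exploratory analysis".

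Table 4 sets the retention benchmark at "> 70% of parents with follow up data" and lists forum use, videos watched and symptom tracking as feasibility metrics. The section on data collection and management says that weekly in-app responses and forum posts are stored. Section {27c} also names an adherence analysis restricted to those who completed the program.

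**The concern.** Intention-to-treat says who is analysed and in which arm. It does not fill in or model an outcome that was never returned, so likelihood does all of that work. With arm, time and earlier scores in the model, likelihood in effect assumes that LightBEAM parents who do not answer would have changed as much as answering LightBEAM parents with the same earlier scores.

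That may fail here. A parent who stops opening the app may also stop answering questionnaires and may gain less. The arms also have different reasons to answer: waitlist parents must complete the re-baselining forms before they get the program, while LightBEAM parents already have it. Use-related dropout at post-intervention is therefore more plausible in the LightBEAM arm, where it would distort the contrast.

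No named analysis tests this. The moderator analysis is exploratory and leaves the primary estimate as it is. The completers-only analysis selects further on engagement, so a larger effect there could be read as a dose response. Yet the trial plans to collect use data that could inform the missing outcomes.

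**Working it through.** The article gives no effect size, SD or missing-data figure to reproduce. The check asks how far an analysis blind to app use would drift under stated assumptions.

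**From the documents:** 1:1 allocation; three waves (pre, post, six-month follow-up); a random-intercept model; a retention benchmark of 70% for follow-up data.

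**Assumed:** half the LightBEAM arm are low users; true average effect 0.30 SD; use unrelated to baseline score; within-person correlation 0.4 to 0.8; waitlist retention 70%; dropout monotone; waitlist mean unchanged over time.

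**Step 1: one post-baseline wave.** Let p_L, p_H be the retention and d_L, d_H the effects in low and high users. The use-blind estimate is the retention-weighted mean

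estimate = (p_L·d_L + p_H·d_H) / (p_L + p_H)

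and its bias is

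bias = (p_H − p_L)(d_H − d_L) / [2(p_L + p_H)].

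Bias is a product of two differences. Both must be non-zero for any bias, and opposite signs reverse it. Examples at 70% mean retention:
- Retention 60%/80%, effects 0.1/0.5: (0.06 + 0.40)/1.4 = 0.329, or +10%.
- Retention 50%/90%, effects 0.1/0.5: (0.05 + 0.45)/1.4 = 0.357, or +19%.
- Retention 50%/90%, effects 0/0.6: 0.54/1.4 = 0.386, or +29%.
- Retention 50%/90%, effects 0.5/0.1: (0.25 + 0.09)/1.4 = 0.243, or −19%.

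**Step 2: three waves.** The benchmark concerns follow-up data, so more parents are assumed to answer at post: (1 + p)/2 for a group with follow-up retention p, which averages 85%. For 50%/90% at follow-up this is 75%/95% at post. With effects 0.1/0.5 the formula gives (0.075 + 0.475)/1.70 = 0.324. The large-sample expectation of the random-intercept likelihood estimate was computed exactly; it agrees at post and supplies the follow-up values. Ranges are over correlations 0.4 to 0.8.

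| Follow-up retention, low/high | Effect, low/high (SD) | Post | Follow-up |
|---|---|---|---|
| 70%/70% | 0.1/0.5 | 0.300 | 0.300 |
| 60%/80% | 0.1/0.5 | 0.312 (+4%) | 0.321–0.324 (+7% to +8%) |
| 50%/90% | 0.1/0.5 | 0.324 (+8%) | 0.342–0.348 (+14% to +16%) |
| 50%/90% | 0/0.6 | 0.335 (+12%) | 0.363–0.371 (+21% to +24%) |
| 50%/90% | 0.3/0.3 | 0.300 | 0.300 |
| 50%/90% | 0.5/0.1 | 0.276 (−8%) | 0.252–0.258 (−16% to −14%) |

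**Step 3: add app use for the LightBEAM arm**, averaged over the randomised mix of users. Every row returns to 0.300 at both waves. This follows from the set-up, in which use fully explains the link between dropout and benefit.

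**Step 4: price.** A separate one-wave simulation of 200 participants assumed 70% LightBEAM and 80% waitlist retention, baseline–outcome correlation 0.6, 60% high users (0.5 SD, 90% retained) and 40% low users (no gain, 40% retained). It gave 0.385 without use and 0.299 with it. The standard error rose from 0.135 to 0.140 (0.140/0.135 = 1.04). Over three such scenarios the increase was 2% to 4%.

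**The case against.** Likelihood under missing-at-random with all randomised participants is a standard choice. Auxiliary variables and sensitivity analyses are detail that a condensed article may leave to an analysis plan that is not shown. That stands: the article's silence is not itself an error, and it nowhere says that only questionnaires enter the likelihood. The point is that a better method than the one named is available from data the trial plans to hold.

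The article also works against the assumed dropout link. Parents are to be reminded to complete questionnaires whatever their participation, and the two $20 payments for post and follow-up carry no stated use condition. These may shrink the bias, but the benchmark still accepts up to about 30% without follow-up data.

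Four stronger readings are tempting and not supported:
- *The effect is overstated.* Low users must both drop out more and benefit less, and the documents give no data on either.
- *The plan expects benefit to depend on engagement.* Aim 2 poses this as an exploratory question.
- *About 30% will be missing at week 12.* The benchmark is a target for follow-up data, a wave the trial design lists separately from post-intervention, and is not split by arm.
- *App records exist for every LightBEAM parent.* Video logs are not among the app-captured data listed in the data-management section, the App Usage item in Table 1 is a questionnaire at post, and partial data are destroyed for withdrawers who refuse their use.

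Nor is the problem invisible: Aim 1 reports use and attrition, and the moderator analysis looks at use and gain. These show the ingredients but do not correct the estimate.

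Finally, the bias can be modest against sampling error. In the Step 4 simulation it is 0.085 against a standard error of 0.135, about 0.6. But bias does not shrink with recruitment: at 500 participants the standard error would be about 0.135 × √(200/500) = 0.085, equal to the bias.

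**Conclusion.** The concern holds conditionally. Likelihood is the only missing-data method named, app use has no stated part in it, and the completers-only analysis cannot show whether use-related dropout distorts the result. If low users both return fewer questionnaires and benefit less, the effect may be overstated by about 4% to 12% at post and 7% to 24% at follow-up in the three-wave model, and by up to about 29% for a single wave at 70% retention with a 50%/90% split. Apart from the 70% benchmark, the retention, effect and correlation inputs are assumptions. The follow-up figures are illustrative also because the waitlist has been offered the program by then, whereas the calculation holds it untreated. The bias is zero without either link and negative if low-use dropouts benefit more. The change is worth making before outcomes are examined, particularly since the data analysts are not blinded.

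**What to change.** In Statistical methods {27a, b} and section {27c}, state that intention-to-treat defines the analysis population and describe missing-data handling separately. Keep all randomised participants and the arm-by-time model.

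- **Missing-data step.** Use multiple imputation by arm, or an equivalent likelihood approach in Mplus, which is already named. For the LightBEAM arm only, include symptom-tracking completion, forum use, and videos watched where logged as auxiliary variables. Prefer completion counts to tracking scores, since the scores are missing for the low users they should inform. Waitlist parents have no app use before post, which is why the step is arm-specific.
- **Efficacy model.** Do not add use as a covariate there; it arises after randomisation.
- **Sensitivity analysis.** Add one in which missing LightBEAM outcomes are imputed from the waitlist distribution. Limit it to the post-intervention contrast, before the waitlist receives the program.

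No new data collection is needed. The cost is wording, modest programming, a standard error about 2% to 4% larger in the simulated cases, and possibly a smaller estimate. The bias is removed only to the extent that recorded use explains the link between dropout and benefit; the sensitivity analysis probes what remains at post.

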### Trial design {12}

Using a two-arm clinical design, participants will be randomized in a 1:1 allocation to be placed in either the 12-week LightBEAM program or the waitlist control. After the 12-week LightBEAM program has been completed by the intervention condition, participants in the waitlist control group will have one month to complete the “re-baselining questionnaires and online orientation prior to gaining access to the LightBEAM intervention. Participants in the intervention condition will complete post-questionnaires at the same time that the waitlist control completes re-baselining questionnaires. Longitudinal self-report questionnaires will be administered digitally at three timepoints: pre-intervention, post-intervention, and at six months follow-up.

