#### Sample size {19}

In total, we plan to recruit a sample of 200–500 Canadians caregivers to participate in the LightBEAM program based on recruitment success over the funding availability period [33]. Sample size was informed by feasibility based on previous BEAM trials (see Simpson et al., [33]).

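### The efficacy model is fixed as random intercepts, which presumes equal variances and correlations over three assessments; if that fails, single-contrast tests can be miscalibrated in either direction

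*Protocol article*

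**What the plan says.** Under Statistical methods {27a, b}, Aim 2, the efficacy model is given as "a multi-level model with random intercepts will be utilized to assess the effect of treatment over time based on conditions". It is to be applied to the primary outcome, where "an individualized composite primary score will be created whereby we examine whether there is a statistically significant change in elevated symptoms of concern" across the assessments, and more generally "we will examine pre-to-post-to follow up program changes in primary and secondary outcomes". On missing values the same section says "Missing data will be address using an intent-to-treat analysis and maximum likelihood estimation".

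Trial design {12} sets the schedule: "Longitudinal self-report questionnaires will be administered digitally at three timepoints: pre-intervention, post-intervention, and at six months follow-up". It does not say whether the six months run from baseline or from the end of the programme. The waitlist arm completes its re-baselining questionnaires after the 12 weeks and then gains access to the app.

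The article does not state how time is coded, does not single out one time point as primary, and gives no SD or within-person correlation. Aim 3 reuses the same multi-level model to ask which families benefit most.

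**The concern.** With three assessments, random intercepts and independent residuals imply compound symmetry: one variance at every time and one correlation for every pair of times. The model then uses a single pooled within-person variance for every change contrast. Repeated symptom scores often depart from this. Distant assessments tend to correlate less than neighbouring ones, and spread can change over time. The pooled variance is then too small for some contrasts and too large for others.

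At stake are the error rate of the treatment-over-time test and the precision of the week-12 comparison. The latter matters because it is the last comparison with an untreated control. The plan also relies on maximum likelihood for incomplete data, with a retention benchmark of only >70%, and likelihood-based estimates lean on the assumed covariance when data are missing.

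**Working it through.** **Inputs.** From the article: random intercepts, three assessments (pre, 12 weeks, six-month follow-up), 1:1 allocation and 200–500 participants. Assumed, because the article gives none: within-person correlations and SDs, two-sided 5% level, and follow-up at week 26 or week 38 (the two readings of the schedule). There is no stated power or error rate to reproduce, since "Sample size was informed by feasibility based on previous BEAM trials".

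**Method (large sample, complete data).** Let S be the true 3×3 covariance and c a contrast over time.
- Pooled within-person variance under random intercepts: s² = [tr(S) − 1′S1/3]/2.
- Modelled variance is proportional to s²·c′c; true variance to c′Sc. Ratio q = c′Sc/(s²·c′c).
- Actual type I error = 2[1 − Φ(1.96/√q)].
- Power, for an effect that gives 80% with the correct variance: Φ(2.80 − 1.96/√q).

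Sample size cancels from q, so the error rates are the same at 200 and 500.

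**Worked example.** Correlations 0.6 (pre–post), 0.6 (post–follow-up), 0.4 (pre–follow-up), all SDs 1.
- tr(S) = 3; 1′S1 = 3 + 2(0.6 + 0.6 + 0.4) = 6.2; s² = (3 − 6.2/3)/2 = 0.467.
- Week 12 minus pre: true 2 − 1.2 = 0.8; modelled 2 × 0.467 = 0.933; q = 0.857. Type I error 3.4%; power 75%.
- Follow-up minus pre: true 2 − 0.8 = 1.2; modelled 0.933; q = 1.286. Type I error 8.4%.

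**Range of assumed covariances.** Linear slope covers weeks 0/12/26 and 0/12/38.

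| Correlations; SDs | Linear slope | Pre to follow-up | Week 12 | Week-12 power (from 80%) | Joint 2-df |
|---|---|---|---|---|---|
| 0.6/0.6/0.6; equal | 5.0% | 5.0% | 5.0% | 80% | 5.0% |
| 0.6/0.6/0.5; equal | 6.6–6.8% | 6.8% | 4.1% | 78% | 5.1% |
| 0.6/0.6/0.4; equal | 8.1–8.4% | 8.4% | 3.4% | 75% | 5.3% |
| 0.6/0.6/0.3; 0.8/1.0/1.1 | 9.5–9.6% | 9.4% | 2.0% | 68% | 5.6% |
| 0.67/0.69/0.52; 1.0/1.04/1.35 | 9.7–9.9% | 9.6% | 1.7% | 66% | 5.7% |
| 0.7/0.7/0.4; 1.0/1.2/1.4 | 11.2% | 11.1% | 1.3% | 63% | 6.1% |
| 0.5/0.7/0.5; equal | 5.4–6.5% | 6.8% | 6.8% | no loss | 5.4% |

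The last row is early divergence followed by stability, and it reverses the week-12 result. The mathematical limit with complete data is q = 2, that is 2[1 − Φ(1.96/√2)] = 16.6%.

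**Second parameterisation.** True random slopes were added, with g = slope variance × SS(time)/residual variance and intraclass correlation 0.5–0.6. Linear-test type I error is 6.3% at g = 0.25, 9.0% at g = 1 and 11.0% at g = 2. The joint test stays at 5.0–6.0%. Week-12 power at N = 200, d = 0.35 falls by about 2–3 points at g = 0.25, 7–13 at g = 1 and 12–23 at g = 2. For example, with intraclass correlation 0.6, g = 1 and weeks 0/12/38, it is 63.7% against 75.3% with the covariance modelled correctly. At g = 0 both models give 79.0%.

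**Simulation check.** With 1,500 trials at N = 200 and 30% missing at follow-up, the linear test rejected 7.9–8.0% (g = 0.5) and 9.2–9.7% (g = 1), the joint test 5.7–6.1% and week 12 2.5–3.7%. A separate simulation with dropout depending on the post score gave 12.1% for the linear test in the 0.67/0.69/0.52 setting, somewhat above the complete-data figure.

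**Spacing.** For 0.6/0.6/0.4 the linear test gives 8.4% with even spacing (0/12/24), 8.4% at 0/12/26 and 8.1% at 0/12/38. Spacing does not drive the result.

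**The case against.** The strongest reply is that the article does not commit to the test that suffers most. It never says time is linear, and its wording about change across assessments fits categorical time at least as well. The joint 2-df test is then nearly correct even under unfavourable covariances. This stands, and it limits the point to linear-slope and single-contrast inference.

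A second reply is that time coding, residual covariance and the type of standard error belong in an analysis plan that is not shown, and that the text does not say random intercepts only. This stands in part: nothing excludes robust standard errors, which Mplus offers. But the article does name the random-effects structure, so this is a stated choice and not merely an omitted detail.

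Third, a reader might take Aim 3 and the engagement analysis as proof that people change at different rates. Those analyses concern differing response to the programme. Under the null, with no effect for anyone, that source of variation is absent, so they are not evidence on the size of any type I error inflation.

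Fourth, the inflation falls mainly on follow-up and slope contrasts, where the waitlist arm has already been given access, while the week-12 error is usually in the safe direction. That is fair, but lost power at week 12 is still a cost.

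**Conclusion.** The concern holds in conditional form. The stated model imposes compound symmetry, and if that fails single-contrast inference can be off in either direction. Over the assumed covariances with complete data, a linear time-by-condition test or the pre-to-follow-up contrast runs at about 5–11%. Week 12 is usually conservative at about 1–4%, with power falling from 80% to roughly 63–78%, and can be slightly liberal at up to about 7%. The effect is therefore nil to moderate, and its size cannot be settled from the article.

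Two stronger readings are tempting and not supported. One is that the primary test certainly rejects too often and week 12 certainly loses power; both depend on unstated time coding and on an unknown covariance, and week 12 is not named as the primary contrast. The other is that uneven spacing causes the problem; the origin of the six months is not stated, weeks 0/12/26 would be nearly even, and equal spacing gives much the same figures.

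**What to change.** In the Aim 2 text, replace the random-intercepts wording with time as a categorical factor and an unstructured within-person covariance over the three assessments, fitted by maximum or restricted maximum likelihood. That is six covariance parameters for 200–500 participants. If the random-intercept form is kept in Mplus, specify robust (MLR) standard errors; these repair the standard errors, but estimates from incomplete data still lean on the assumed covariance. State the time coding and the origin of the six-month follow-up in the same edit.

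The cost is a line or two of wording, a few more covariance parameters, and possibly slightly less favourable slope or follow-up p-values. If compound symmetry is true, essentially nothing is lost: week-12 power was 79.0% under both models at N = 200, d = 0.35, and 87.8% under both at N = 500, d = 0.25 (intraclass correlation 0.6). The change is best made before the interim analysis planned after the first 100 completers, because the analysts are not blinded and a later change would look data-driven.

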##### Eligibility screener (Main Participants Only)

All primary participants will complete an online eligibility screener to determine if they meet the required inclusion criteria. The eligibility screener consists of several standardized measures to assess depression, anxiety, parenting stress and anger. The Generalized Anxiety Disorder questionnaire (GAD-7; Spitzer et al. [35]) and the Patient Health Questionnaire (PHQ-9 [16]) will be used to examine parental anxiety and depression respectively. These questionnaires ask parents to reflect upon mental health concerns in the past two weeks. Both the GAD-7 (α = 0.92) and the PHQ-9 (α = 0.88) evidence robust internal reliability [16, 35]). The Parenting Stress Index Short Form (PSI-SF) is a 36-item questionnaire that will be used to assess parenting stress. The PSI asks parents to report on a variety of factors including parental distress, parent–child dysfunctional interactions, and difficult child behaviour (e.g., I feel trapped by my responsibilities as a parent; α = 0.87; Abidin et al. [1], Barroso et al. [5]). The Patient Reported Outcomes Measurement Information Symptom [PROMIS] Anger scale will be used to evaluate parenting anger. This ten-item scale asks parents to reflect on experiences of anger in the past seven days (e.g., I was irritated more than people know; α. = 88; Kaman et al. [14]).

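### As usually fitted, the Aim 2 model gives the post-intervention effect a change-score variance; constraining baseline means to be equal would gain precision at no data cost

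*Protocol article*

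**What the plan says.** The Aim 2 text under Statistical methods names the model: "a multi-level model with random intercepts will be utilized to assess the effect of treatment over time based on conditions". It then states the target: "we will examine pre-to-post-to follow up program changes in primary and secondary outcomes". The primary outcome is built from the scales on which a person screened in: "an individualized composite primary score will be created whereby we examine whether there is a statistically significant change in elevated symptoms of concern". Under Trial design, the waves are given as "Longitudinal self-report questionnaires will be administered digitally at three timepoints: pre-intervention, post-intervention, and at six months follow-up", and "participants will be randomized in a 1:1 allocation".

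On this wording the pre-intervention score enters as one of the repeated outcomes. The text does not say whether baseline means are estimated separately by arm or held equal, and it does not list the baseline score as a covariate. The only adjustment variable the article names for the analyses is use of other services (Tracking concomitant care).

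The baseline information exists. "The eligibility screener consists of several standardized measures to assess depression, anxiety, parenting stress and anger", and Table 1 marks the same four scales again at pre-intervention for main participants. Missing data are to be handled by maximum likelihood with all randomized participants included.

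On size, the article says "we plan to recruit a sample of 200–500 Canadians caregivers", and "Sample size was informed by feasibility based on previous BEAM trials". It gives no power, effect size, standard deviation or correlation.

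**The concern.** A random-intercept model with free baseline means and a condition-by-time term estimates, at post-intervention, the difference between arms in change from baseline. That fixes the coefficient on the baseline score at 1. With equal variances over time, the best coefficient is the pre-post correlation, which is below 1. The change contrast therefore carries extra noise, and in any one trial it over-corrects a chance imbalance at baseline.

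Precision is at stake. The sample size is set by feasibility and spans a 2.5-fold range (500/200), so the choice of analysis is the cheapest way to narrow the confidence interval. The Blinding section also says that data analysts know the allocation, which is a reason to settle the handling of baseline in advance.

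**Working it through.** There is no figure in the article to reproduce.

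**Inputs from the article:** 1:1 allocation; 200 to 500 in total, so 100 to 250 per arm; three waves; maximum likelihood on all randomized; a retention benchmark above 70% (Table 4), used here as a scenario of 30% missing.

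**Assumptions not in the article:** pre-post correlation rho from 0.4 to 0.7; equal variances at all waves (SD = 1); time as categories; the 30% missing in each arm at both post and follow-up; two-sided 5% and 80% power, so a multiplier of 1.96 + 0.84 = 2.80.

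**Step 1, complete data.** Per-arm variance factors are 2(1 − rho) for the change contrast and 1 − rho² when baseline is conditioned on. Their ratio is (1 + rho)/2, so the saving is (1 − rho)/2.

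**Step 2, maximum likelihood with missing data.** With n randomized and m observed at post per arm, the variance of the effect is

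- baseline means free: 2[(1 − rho²)/m + (1 − rho)²/n]
- baseline means equal: 2(1 − rho²)/m

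With n = 100 and m = 70:

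| rho | Change factor | Adjusted factor | Saving, complete | Variance, free | Variance, equal | Saving, 30% missing |
|---|---|---|---|---|---|---|
| 0.4 | 1.20 | 0.84 | 30% | 0.0312 | 0.0240 | 23% |
| 0.5 | 1.00 | 0.75 | 25% | 0.0264 | 0.0214 | 19% |
| 0.6 | 0.80 | 0.64 | 20% | 0.0215 | 0.0183 | 15% |
| 0.7 | 0.60 | 0.51 | 15% | 0.0164 | 0.0146 | 11% |

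An exact generalized-least-squares calculation for the three-wave random-intercept model gives the same values, with complete data and with 30% missing. Over a wider range, rho 0.3 to 0.8, the saving runs from 35% to 10% with complete data and from 27% to 7% with 30% missing.

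**Step 3, detectable difference at rho = 0.5 and 70% retention.**

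- N = 200, free: 2(0.75/70 + 0.25/100) = 0.0264; 2.80 × √0.0264 ≈ 0.46.
- N = 200, equal: 2 × 0.75/70 = 0.0214; 2.80 × √0.0214 ≈ 0.41.
- N = 500, free: 2(0.75/175 + 0.25/250) = 0.01057; 2.80 × √0.01057 ≈ 0.29.
- N = 500, equal: 2 × 0.75/175 = 0.00857; 2.80 × √0.00857 ≈ 0.26.

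The variance ratio is 0.0264/0.0214 ≈ 1.23, equivalent to about 23% more participants.

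**Scope.** The calculation concerns the post-intervention contrast only. Under Trial design, the waitlist arm completes its re-baselining questionnaires when the intervention arm completes its post-questionnaires, and then gains access to the program. A later contrast no longer compares program with no program.

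**The case against.** The strongest objection is that the article does not fix the choice. A model with baseline means held equal is also a random-intercept multilevel model of treatment over time, and speaking of change from pre to post fits either form. A condensed article may leave this to a full plan that is not shown, and if that plan constrains the means, the loss is zero. This stands as a condition on the point. It does not remove it: the article states a model and a change target, whose ordinary reading is free baseline means, and it names one adjustment variable without naming the baseline score.

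It is also fair to say that both analyses are standard and valid. A reader might infer that the planned estimate is biased. It is not: under randomization the change contrast is unbiased, and only precision is lost.

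Three further readings go beyond the documents:

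- A reader might take 15% to 30% as a share of the variance reduction that baseline could provide. It is the fall in the variance of the effect relative to the change contrast, with complete data and assumed correlations. As a share of the attainable reduction (rho²), the loss would be (1 − rho)²/rho², which is 18% at rho 0.7 and 100% at 0.5.
- A reader might apply the complete-data ratio at rho 0.5 (1.00/0.75) and claim the equivalent of 33% more participants. With 30% missing, that describes a completers-only change analysis, whereas the plan uses maximum likelihood on everyone randomized. The figure is then about 23%.
- A reader might argue that selecting people with elevated scores lowers rho and so enlarges the penalty. The documents do not support this. Selection is on the screener, not on the pre-intervention score. The excess variance of a change score is the baseline variance times (1 − slope)², which shrinks as the baseline spread narrows if the slope is stable. The direction depends on covariances that the article does not give.

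Finally, a plain regression of the post score on baseline among those observed would drop randomized participants, against the stated intent-to-treat approach. That is a reason to prefer the constrained longitudinal model.

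**Conclusion.** The point holds as an avoidable loss of precision, conditional on the model being fitted in its usual form with free baseline means. Under the planned estimator with 30% missing, the variance of the post-intervention effect could be lowered by about 23% at rho 0.4, 19% at 0.5 and 11% at 0.7. With complete data the range is 30% to 15%. These sizes rest on assumed correlations and equal variances. Within the correlations examined the direction does not change. This is a worthwhile improvement to the analysis, not an error that invalidates it.

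**What to change.** State in the Aim 2 text that the multilevel maximum-likelihood model on all randomized participants constrains pre-intervention means to be equal across arms, so that the condition effect enters only at post-baseline times. State also that the efficacy contrast is the condition difference at post-intervention, with the waitlist arm's re-baselining questionnaire as its value at that time. The screener score may be added as a covariate for main participants. If the full plan already does this, the article needs only to say so.

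One limit should be noted in the text. Co-parents complete no screener, and Table 2 marks no pre-intervention Parenting Stress Index for them, so the full gain applies to main participants.

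The cost is a change of analysis wording. No new data are needed.
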